#### UKA — unicompartmental knee arthroplasty

Oxford® Partial Knee (Zimmer Biomet, Warsaw, IN, USA) arthroplasty (PKA) is performed from medial parapatellar arthrotomy without dislocating the patella. Tourniquet is used for every patient if no contraindications exist. Retropatellar fat pad is partially resected if necessary, to ensure adequate surgical visualization. The anterior cruciate ligament is inspected for possible ligament rupture and fibrillation, and lateral and patellofemoral joint compartments are inspected for possible cartilage damage. Patients with lateral OA grade II or greater are excluded from the study at this point. Grade of medial femoral and tibial cartilage loss is verified. All osteophytes are removed from the intercondylar notch, medial margin of the medial condyle, tibial plateau, and patella. PKA instrumentation and implantation are performed according to the cementless Oxford® PKA Microplasty® (Zimmer Biomet, Warsaw, IN, USA) instrumentation system technique. Local infiltration analgesia is used for all patients. The wound is closed in a standard manner. An elastic bandage is applied. Full weight-bearing is allowed immediately after the surgery [21].

### Outcomes

The outcomes of this study consist of objective and patient-reported outcomes. The outcomes will be collected at randomization, preoperative visit, and postoperatively 3, 6, and 12 months. We will follow up the participants thereafter at 2, 5, and 10 years via letter survey.

#### Baseline data

Baseline data is collected at the time of randomization at the outpatient clinic. These include radiographs of the affected knee, weight-bearing mechanical axis, MRI, KOOS_5,_ Lysholm, Oxford knee score, and Osteoarthritis Research Society International (OARSI) performance-based measures. The patients receive an activity watch (Withings Move®, Issy-les-Moulineaux, France), which they are asked to use day and night throughout the trial.

#### Primary outcome measure

The Knee Injury and Osteoarthritis Outcome Score (KOOS) is a validated patient-reported outcome measure (PROM) assessing the outcomes of various knee conditions [22]. The tool consists of five subscales: pain, other symptoms, activities of daily living, function in sports or recreational activities, and quality of life. We will use the KOOS_5_ composite score as the primary outcome measure. Based on clinical experience and literature, there will be only minimal change in pain and PROM scores after 1 year postoperatively [23]. Thus, the primary outcome measure, KOOS_5_ score for HTO vs. UKA is analyzed 12 months postoperatively. A minimal clinically important difference (MCID) of 10 points will be used [24].

#### Secondary outcome measures

Secondary outcome measures are divided into objective (OARSI, length of stay, Withings activity measures, Radiographs [KL and OA progression]), patient-reported (KOOS subscales, pain visual analog scale [VAS], Lysholm, and Oxford knee scores), and adverse events (conversion to TKA, complications [peri- and postoperative], need for revision surgery) outcomes.

In addition to KOOS_5_, additional PROMs are gathered from the Lysholm score (MCID, 4.2 points) [25] and Oxford knee score (MCID, 5 points) [26]. We will also report KOOS subscales individually (ADL, Pain, Symptoms, Quality of life, Sport/Rec) [27].

Average pain for the previous 2 weeks is measured using VAS, which is validated to knee OA pain (MCID, 17 mm) [28, 29].

The OARSI performance-based tests are performed by a physical therapist at baseline and at follow-up visits as shown in the participant timeline in Table 2. This includes 30-s chair stand test (MCID, 2 repetitions), 40-m fast-paced walk test (MCID, 0.2 m/s), stair climb test (MCID, 5.5 s), the timed up and go test (MCID: reduction of 0.8 s), and 6-min walk test (MCID, 20 m increase) [30].

**Table 2 Tab2:**
[figure not shown]
Participant timeline of the trial

After the surgery, the days spent in the hospital will be recorded to follow the early recovery. Early readmissions within 90 days after surgery for any reason are reported for the analysis of possible complications. See safety considerations for the list of complications monitored.

The OA progression is monitored at the follow-up visits using radiographs of the knee at 3, 6, and 12 months after surgery, and the mechanical axis is re-evaluated at 12 months post-randomization. Patients not satisfied with the results of operative treatment (HTO or UKA) can be converted to TKA at any time during the follow-up.

For later determining the MCID of KOOS_5_ in this study, we will include an anchor question to the trial: “If you think about your pain level and daily activities this week, would it be acceptable that your knee would be like this for the rest of your life?”. The answer options are “Yes” or “No.” The proportion of patients reaching the Patient Acceptable Symptom State (PASS) be analyzed from the answers to this question.

We will use the Withings Move electronic watch as an activity tracker. The watches are given to patients right after randomization and the patients are asked to wear them for 24 h per day until the primary time-point of 12 months. The following data are recorded: ID number, date, time, number of steps per day, and sleeping hours. The watch is connected to a secured database and the data is wirelessly transferred and stored.

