### Sample size

The sample size calculation was performed using G*Power 3.1 and was based on KOOS_5_ as the primary outcome measure in this trial. For the sample size calculation, we used a two-sided α level of 0.05. We assumed the MCID of the KOOS_5_ to be 10 points, [27, 31] with an SD of 15 points. Using these assumptions, the required sample size is 36 per group with 80% power to show a clinically important difference between the treatment methods with a two-sided type I error rate of 5%. With the assumption of 36% lost to follow-up, we decided to include 50 participants per group.

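### The anchor question said to determine the KOOS5 MCID asks whether the present state is acceptable, so it supports PASS and not a minimal important change

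*Protocol article*

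**What the plan says.** The text after Table 2, within the protocol article's section on secondary outcome measures, gives the purpose of the item: "For later determining the MCID of KOOS_5_ in this study, we will include an anchor question to the trial". The item refers to pain and daily activities in the current week and asks: "would it be acceptable that your knee would be like this for the rest of your life". Patients answer Yes or No. One analysis of the answers is then stated: "The proportion of patients reaching the Patient Acceptable Symptom State (PASS) be analyzed from the answers to this question".

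Elsewhere the MCID is fixed in advance. The section on the primary outcome measure says "A minimal clinically important difference (MCID) of 10 points will be used [24"], and the sample size section says "We assumed the MCID of the KOOS_5_ to be 10 points, [27, 31] with an SD of 15 points". Neither figure comes from the anchor question. The text describes no item asking how the knee has changed since before surgery.

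**The concern.** An anchor-based MCID needs an external judgement of change. Patients say whether, and by how much, they are better or worse, and the score change in those reporting a small but worthwhile improvement is estimated. The printed item does not mention baseline, change or importance, and it has no category for a small improvement. It sorts patients by their present state. The stated purpose is therefore an MCID, while the wording, response scale and stated analysis are those of PASS.

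The hypotheses and expectations of this trial are worded in terms of clinically important differences, so a figure published as the trial's own KOOS5 MCID could be taken up by readers. If it came from this item, it would be mislabelled. Ratings of change not asked at a visit are also hard to recover afterwards.

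**Working it through.** **1. The plan's own figure.** The only calculated figure that uses the KOOS5 MCID is the sample size. Inputs from the sample size section are a difference of 10, an SD of 15, two-sided α of 0.05 and 80% power.

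n per group = 2(z₀.₉₇₅ + z₀.₈₀)² × SD²/δ² = 2 × (1.960 + 0.842)² × 15²/10² = 2 × 7.85 × 2.25 = 35.3, rounded up to 36.

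The t-test version gives 36.3, with 79.7% power at 36 per group. The plan states "the required sample size is 36 per group with 80% power", so the figure reproduces. No input comes from the anchor, and nothing here changes if the anchor is corrected.

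**2. What the answer measures.** Let B be the baseline score, F the follow-up score, C = F − B the change, and T the score at which a patient finds the state acceptable. The answer is Yes when F ≥ T, which is the same as C ≥ T − B. The change that turns No into Yes is therefore T − B. It depends on where the patient started and on T, and nothing makes it minimal.

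Two invented patients with T = 70 show this:
- 40 to 60: a change of 20, below T, answers No.
- 68 to 71: a change of 3, above T, answers Yes.

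**3. How far a change cut-off could be off.** The documents give no KOOS5 baseline, expected gain or acceptability threshold, so all inputs here are assumptions. Baseline has mean 40 and SD 15. Change has SD 15 and mean 20, 30 or 40. T is 55, 65 or 75. Patient judgement carries noise of SD 7. Scores are not capped, and 60,000 patients are simulated per setting. The state anchor is Yes when noisy F ≥ T. The comparison anchor is Yes when noisy C ≥ 10, so the built-in important change is 10. The cut-off on C is the value that maximises sensitivity + specificity − 1 (Youden).

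| T | Mean gain | Cut-off on change, state anchor | Cut-off on follow-up score, state anchor | Cut-off on change, change anchor |
|---|---|---|---|---|
| 55 | 20 | 18.5 | 56.5 | 14.0 |
| 55 | 30 | 25.5 | 59.5 | 18.5 |
| 55 | 40 | 33.5 | 63.0 | 23.0 |
| 65 | 20 | 20.5 | 63.0 | 14.5 |
| 65 | 30 | 29.0 | 66.5 | 18.0 |
| 65 | 40 | 35.5 | 70.0 | 23.5 |
| 75 | 20 | 24.0 | 70.5 | 14.5 |
| 75 | 30 | 32.0 | 73.5 | 18.5 |
| 75 | 40 | 39.0 | 77.0 | 23.0 |

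With the state anchor, the change cut-off runs from 18.5 to 39 and rises with both the mean gain and T. Because F = B + C and scores are uncapped, raising T by 10 has the same effect on this cut-off as lowering mean baseline by 10. The three T blocks can therefore be read as baseline means of 50, 40 and 30 at T = 65. The follow-up score cut-off, 56.5 to 77, is a PASS threshold, which is what the item can deliver. The change anchor also overshoots 10, at 14 to 23.5, and rises with mean gain. It does not depend on T beyond 0.5 points, which is the grid step.

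**4. Precision of a change anchor in this trial.** Assume 10 to 15 of the 100 patients report a slight improvement, and borrow the plan's SD of 15 for change. The 95% half-width is t × SD/√n:
- n = 10: 2.262 × 15/3.162 = 10.7 points
- n = 15: 2.145 × 15/3.873 = 8.3 points

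An estimate near 10 would carry an uncertainty of about its own size.

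**The case against.** The strongest reply is that no conclusion of the trial depends on this sentence. The 10-point MCID is set from the literature. The primary result is a mean difference with confidence interval and p-value, and Table 3 lists neither an MCID derivation nor PASS as an outcome. The MCID work is described as something for later. The one analysis stated for the answers, the PASS proportion, is one that the question supports. All of this stands and limits the weight of the point.

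A reader might infer that an inflated trial-specific MCID will displace the 10 points and make a real difference between the arms look unimportant. The article does not support that, because nowhere does it plan to replace the prespecified value. A reader might also pick one pair of scores, such as baseline 40 and threshold 70, and announce a 30-point MCID. That rests on values the article does not give, and only a range under stated assumptions is defensible.

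Two further replies stand in part. A change cut-off can be calculated against a Yes/No state question, so it is too strong to say that no number could be produced; the number would answer a different question. And Table 2 is not shown, while the article condenses a fuller protocol, so another anchor listed only there cannot be excluded. Neither reply removes the mismatch, because the article prints this question and gives it the MCID purpose.

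Finally, a change anchor is no complete cure: in the simulation it also overshot 10, and the informative group may be small.

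**Conclusion.** The point holds in a limited form. As printed, the question serves PASS, and the purpose of determining the KOOS5 MCID is wrongly assigned to it. This follows from the wording alone and needs no assumed figures. The 18.5 to 39 range against a built-in 10 shows direction and instability only. It rests on assumed baseline, gain, threshold and noise, and is no forecast for this trial.

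The sample size, the primary analysis and the prespecified 10-point threshold are untouched. What is affected is the later MCID derivation and any reading of the results against it. The point is worth correcting because the remedy is small and, if a change item is wanted, its value falls with every visit that passes without it.

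**What to change.** Keep the present question, use it for PASS only (proportion and, if wanted, a KOOS5 score threshold), and reword the sentence that assigns it to the MCID. This costs one edited sentence and needs no new data.

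Then choose one of two courses:

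- **If a trial-specific MCID is still wanted**, add one global rating-of-change item with 5 or 7 graded levels, comparing the knee with its state before surgery, at the existing 3-, 6- and 12-month visits. Derive the MCID from the category of slight improvement and report it with its confidence interval and the number of patients in that category. The cost is one line on the paper forms in both study languages, a small patient burden, and a protocol change entered in the registry. The article was published in April 2023 with a start planned for the first half of that year, so it cannot be confirmed that the item could be in place for the first patients. The category may also be too small for a precise estimate.
- **Otherwise**, delete the MCID purpose.

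Under either course, state that the prespecified 10 points remains the threshold for interpreting the between-group difference in KOOS5 at 12 months.

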#### Cost-effectiveness

The consumption of healthcare and social services, used implants, pain medication, and alternative medical services and all related costs will be included in the cost-effectiveness analysis. The costs and benefits will be evaluated against the difference in our primary outcome and in the results of the KOOS quality of life subscale. Used implants, pain medication, and consumption of alternative therapies (i.e., osteopath, chiropractor, naprapath, healer) will be recorded.

The outcome measures are summarized in Table 3.

**Table 3 Tab3:** Outcome measures

**Primary outcome measure**
1. KOOS_5_ at 12 months postoperatively
**Secondary outcome measures**
1. KOOS subscales (pain, symptoms, activities of daily living, function in sports or recreational activities, and quality of life)
2. Average pain for the last 2 weeks (VAS 0–100 mm)
3. Lysholm and Oxford knee score
4. The 2013 OARSI recommended set of performance-based tests of physical function (i.e., 30-s chair stand test, 40-m fast-paced walk test, stair climb test, the timed up and go test, and 6-min walk test)
5. Days spent in hospital, readmission 90 days
6. Withings Move activity results
7. Radiographic progression of the arthrosis (KL grade mean) at 12 months
8. Changes in mechanical axis at 12 months (degrees from neutral axis)
9. Complications
10. Cost-effectiveness
11. Re-operation
12. Conversion to TKA

### Safety considerations

Adverse surgical complications (deep wound infection, deep venous thrombosis, mechanical failure, post-operative fracture, neurologic complication) and minor complications (superficial wound infection, pain) are collected and reported in the results.

### Sample size

The sample size calculation was performed using G*Power 3.1 and was based on KOOS_5_ as the primary outcome measure in this trial. For the sample size calculation, we used a two-sided α level of 0.05. We assumed the MCID of the KOOS_5_ to be 10 points, [27, 31] with an SD of 15 points. Using these assumptions, the required sample size is 36 per group with 80% power to show a clinically important difference between the treatment methods with a two-sided type I error rate of 5%. With the assumption of 36% lost to follow-up, we decided to include 50 participants per group.

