### Interventions

After recruitment, the patients are scheduled an appointment with a physical therapist and an individual training program is introduced. Patients are randomized to either HTO or UKA in 1:1 ratio. If the patients’ symptoms are reduced markedly before the operative treatment (1–4 months post randomization) a possibility for drop-out is offered. Both UKA and HTO operations are performed by experienced surgeons with at least 50 operations of UKA or HTO in total.

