### Statistical analyses

We will conduct all primary and secondary analyses according to the intention-to-treat principle. The Consolidated Standards of Reporting Trials statement will be used in the reporting of the trial results [32].

We will conduct the primary comparison (KOOS_5_ composite score) between the study groups using a mixed-model repeated-measures analysis of variance (MMRM ANOVA) allowing possible data missingness. We will assume data missing at random. Study group and time of assessment will be used as fixed factors and patients will be used as random factors. We are using the model to quantify the treatment effect as the absolute difference between the groups in KOOS_5_ (mean and 95% confidence interval [CI]) and *p*-value at 12 months postoperatively. A two-sided *p*-value of 0.05 will be used to indicate statistical significance.

We will compare secondary outcomes using a similar model where applicable (e.g., KOOS subscales, pain-VAS, Lysholm, Oxford knee score, OARSI). Radiological classification (KL- classification) is used for covariate in post hoc analysis. For categorical response variables, we will analyze the effects using the generalized estimating equations model with the unstructured correlation structure. Secondary outcomes will be considered explanatory and/or exploratory. Thus, multiplicity is not considered a problem. We will report adverse events descriptively.

We plan to perform a sensitivity analysis according to as-treated principle where the patients are analyzed according to their definitive treatment method irrespective of the randomization.

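### Fifty per group tolerates 28% loss to follow-up, not the stated 36%; at 36% loss the power, on the protocol's own basis, is about 75% rather than 80%.

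*Protocol article*

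**What the plan says.** In the protocol article, the Sample size section bases the calculation on KOOS5. On the error rate it says "we used a two-sided α level of 0.05", and it assumes a minimal clinically important difference of 10 points "with an SD of 15 points". The Primary outcome measure section gives the same difference: "A minimal clinically important difference (MCID) of 10 points will be used". Allocation is equal (Interventions: "Patients are randomized to either HTO or UKA in 1:1 ratio").

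From these inputs the Sample size section concludes that "the required sample size is 36 per group with 80% power to show a clinically important difference between the treatment methods". It then moves from the number required to the number enrolled in one sentence: "With the assumption of 36% lost to follow-up, we decided to include 50 participants per group". No inflation formula and no other loss rate is given. The Abstract repeats 50 per arm, 100 in total.

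**The concern.** Three linked figures stand next to each other: 36 required, 36% lost, 50 enrolled. Any two of them fix the third, and the third does not agree.

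The allowance for loss is what carries the stated 80% power from the evaluable patients to the enrolled ones. If it is wrong, a reader is given a larger safety margin than the trial has. This matters more than usual here because the Expectations section anticipates no clinically relevant difference between the procedures. For a trial expected to report no difference, the type II error rate largely decides how convincing that result will be, so it should be stated correctly at the loss the trial itself assumes.

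**Working it through.** **Inputs** (Sample size section unless noted): difference 10 points; SD 15, so d = 10/15 = 0.667; two-sided α 0.05; power 80%; 36 evaluable per group; 36% loss; 50 enrolled per group; 1:1 allocation (Interventions).

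**Step 1. Reproduce the 36.**

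Normal approximation: n = 2(z₀.₉₇₅ + z₀.₈₀)²/d² = 2(1.96 + 0.8416)²/0.6667² = 35.3, so 36 per group. The stated figure reproduces. The exact two-sample t-test solution is 36.3, so 37 per group, and its power at 36 is 79.7%. That one-patient difference is immaterial and is not the point raised here.

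**Step 2. Try to reproduce the 50.**

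- To keep n evaluable after a proportion L is lost, enrol n/(1 − L). Here 36/(1 − 0.36) = 36/0.64 = 56.25, so 57 per group, or 114 in total. Starting from 37, it is 37/0.64 = 57.8, so 58 per group, or 116 in total.
- Check: 56 × 0.64 = 35.84, which is too few; 57 × 0.64 = 36.48, which is enough.
- The stated 50 does not reproduce. It is seven per group short, which rounding cannot explain.

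**Step 3. What 50 per group does allow.**

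- Loss absorbed while leaving 36: 1 − 36/50 = 28%. If 37 are needed: 1 − 37/50 = 26%.
- Patients left after 36% loss: 50 × 0.64 = 32 per group.

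**Step 4. Power at each retained number.** Two-sample t-test with noncentrality d√(n/2), and the normal approximation Φ(d√(n/2) − 1.96):

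| Loss from 50 | Retained per group | Power, t-test | Power, normal |
|---|---|---|---|
| 0% | 50 | 91.0% | 91.5% |
| 26% | 37 | 80.8% | 81.8% |
| 28% | 36 | 79.7% | 80.7% |
| 30% | 35 | 78.5% | 79.6% |
| 36% | 32 | 74.7% | 76.0% |

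For n = 32 the noncentrality is 0.667 × √16 = 2.667, and Φ(2.667 − 1.96) = 0.760.

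**Step 5. A possible origin.** Multiplying by (1 + L) instead of dividing by (1 − L) gives 36 × 1.36 = 48.96, or 37 × 1.36 = 50.3. Both are close to 50. The article does not state its formula, so this is only a guess, and nothing above depends on it.

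**The case against.** **The mixed model uses patients who leave early.** This is the strongest objection. The Statistical analyses section plans a repeated-measures mixed model and says "We will assume data missing at random". The Outcomes section schedules assessments at randomization, before surgery, and at 3, 6 and 12 months. A patient without a 12-month score can therefore still contribute, and the 74.7% is a completers-only figure.

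The possible gain can be sketched, but only under an assumed correlation r between an earlier score and the 12-month score, because the article gives none. If 32 of 50 per group have the 12-month score and all 50 have the earlier one, the effective number per group is 1/[(1 − r²)/32 + r²/50]:

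- r = 0.3: 33.1, power about 76%
- r = 0.5: 35.2, power about 79%
- r = 0.6: 36.8, power about 80.5%

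So 75% is the low end under the planned model. This softens the size of the shortfall. It does not repair the sentence, because the sample size calculation claims no credit for repeated measures. Patients lost early would also have only pre-operative scores to contribute, and their correlation with the 12-month result is unknown.

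**The 36% may be pessimistic, or a misprint.** Either is possible. If actual loss stays at or below 28%, power is about 80% or better and nothing is lost. If the percentage was mistyped, the enrolment figure may be right and only the loss rate wrong. The printed figures still conflict and need correcting.

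**The correction changes nothing in the conduct of the trial.** True if the loss rate is restated and 50 per group is kept. The point concerns a misstated tolerance in the justification for the primary outcome, not a failed design. A margin for loss exists; its size is wrong.

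**Conclusion.** The concern holds. With 36 evaluable patients required, 50 per group covers a 28% loss, not 36%. At the trial's own assumed loss, 32 per group remain and power for a 10-point difference is 74.7% by t-test, or 76.0% by normal approximation. The type II error is then about 25% instead of 20%.

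The retention arithmetic uses only figures printed in the Sample size section. The power figures also rest on the protocol's SD of 15, equal loss in the two groups, and a comparison of patients with 12-month data, which is the basis of the protocol's own calculation. No other section repairs the inconsistency.

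The article does not say whether the 36% includes the post-randomization drop-out option (Interventions) and the exclusions made at surgery (Surgical technique). If it does not, those losses use up the same 28%.

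**What to change.** Keep 50 per group and replace the final sentence of the Sample size section with wording such as:

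> Enrolling 50 per group retains 36 evaluable participants per group with up to 28% loss (about 80% power). If loss reached 36%, 32 per group would remain and power would be about 75%.

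This costs one sentence and no patients; the only price is a less favourable stated tolerance. It would help to say in the same place which losses the percentage covers.

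If the sponsor regards 36% as realistic and wants to hold the stated power, the alternative is to enrol 57 per group (114 in total), or 58 (116 in total) if 37 evaluable are required by the exact t-test. That is 14 to 16 more participants.

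The Protocol amendments section says that changes are updated at ClinicalTrials.gov, so the correction should be carried there too. The registry record was not available for this review, so whether it repeats the 36% needs checking.
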